### Statistical analysis

The sample size was based on the run shuttle walk test levels and on the maximum load achieved in CPET [14]. Considering the stages of the shuttle, and assuming an alpha risk of 5 % and beta risk of 80 %, standard deviation of 1.6, and a difference in magnitude of 2.0 levels before and after the pulmonary rehabilitation program [14], the sample size needed was 27 patients in each group. Considering the load (W) achieved in the cardiopulmonary exercise testing, with a −3 ± 2 W difference pre- and post-intervention in the control group, and of 16 ± 7 [20] in the intervention group, with an alpha risk of 5 % and a beta risk of 95 %, the sample size needed was 10 patients in each group. Therefore, considering potential losses, 30 asthmatic patients will be recruited for each group, requiring a total of 66 volunteers.

The data normality will be analyzed using the Kolmogorov-Smirnov test. Parametric data will be represented as means (SD) and nonparametric data as medians (IQR (25th−75th percentiles ). Comparisons between groups and time (pre- and post-rehabilitation) will be analyzed by two-way analysis of variance (ANOVA), with the Bonferroni test post hoc, or by the Kruskal Wallis test, depending on the data adherence or non-adherence to the Gaussian curve. Correlation between variables will be analyzed by Pearson or Spearman correlation according to the data distribution. Three-way repeated measures ANOVA group vs endurance (0–100 % endurance time, 25 % increments time) vs time (pre- and post-) will be used to assess the dependency of the EMG variables and will followed by post hoc Student–Newman–Keuls pairwise comparisons, when appropriate. The value of *P* <0.05 will be set as significant. SPSS version 13 (Chicago, IL, USA) will be the statistical software used in the study.

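### The main ANOVA and its post hoc tests use one pooled error, although the plan's own CPET load figures imply a variance ratio of about 12 between arms

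*Protocol article*

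**What the plan says.** All the relevant text is in the protocol article, Statistical analysis.

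- **Main analysis:** comparisons between the groups and over time, before and after rehabilitation, "will be analyzed by two-way analysis of variance (ANOVA), with the Bonferroni test post hoc". Kruskal-Wallis is the alternative for data that are not Gaussian. The only distributional check named is Kolmogorov-Smirnov, for normality.
- **CPET load, used for sample size:** "with a −3 ± 2 W difference pre- and post-intervention in the control group, and of 16 ± 7 [20] in the intervention group". The ± is not labelled; I read it as an SD.
- **Shuttle test, used for sample size:** "standard deviation of 1.6, and a difference in magnitude of 2.0 levels before and after the pulmonary rehabilitation program". This is a single SD, with no split by arm.
- **EMG analysis, for contrast:** "Three-way repeated measures ANOVA group vs endurance (0–100 % endurance time, 25 % increments time) vs time (pre- and post", and so on. Repeated measures is named here but not for the main two-way ANOVA.

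The Outcomes section makes CPET and the ISWT together the primary outcome. Arms are planned equal. The Study design section excludes children who miss more than 20% of sessions, and the sample size allows for losses without giving a rate.

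**The concern.** A two-way ANOVA and its post hoc tests use one residual variance for everyone. If training makes children respond by differing amounts while controls hardly change, which is what ±7 W and ±2 W describe, that single variance fits neither arm. It is too small for the training arm and too large for control. Standard errors, intervals and p-values for the within-arm changes are then wrong in opposite directions. The between-arm comparison, which answers the trial's question, keeps its level only while the arms are equal in size.

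The normality check would not catch this: data can be Gaussian in each arm with SDs of 2 and 7. So the point is not a detail left for later. A stated method conflicts with the planning figures printed beside it.

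**Working it through.** **Inputs (Statistical analysis section).** SD of change in load: 2 W control, 7 W training. Significance level 0.05, taken as two-sided. 30 per arm.

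**The plan's own figure.** The two SDs appear only in the calculation that ends "with an alpha risk of 5 % and a beta risk of 95 %, the sample size needed was 10 patients in each group". With a difference of 16 − (−3) = 19 W, these SDs and 95% power (taking the stated beta risk as power), I get 2 per group by the normal formula or 4 by the t distribution, not 10. That is a separate problem, and nothing below depends on it.

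**1. Size of the mismatch, repeated-measures reading.**
- Variance ratio: 49/4 = 12.25.
- Pooled SD of change with equal arms: √((4 + 49)/2) = √26.5 = 5.15 W.
- Training: 5.15/7 = 0.735, so 26% too small. Control: 5.15/2 = 2.57, so 2.6 times too large.

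**2. Training-arm pre-post test, no true change, 30 per arm.** The test rejects when |mean change| exceeds c × 5.15/√30, but the true standard error is 7/√30. The effective threshold is therefore 0.735c, with c from t on 58 df. The pooled variance itself behaves like one on (49 + 4)²/[(49² + 4²)/29] = 33.7 df.

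| Bonferroni comparisons | Nominal | c | 0.735c | Tail area, t on 33.7 df | Simulated |
|---|---|---|---|---|---|
| 2 | 2.5% | 2.301 | 1.692 | 10.0% | 9.9% |
| 6 | 0.83% | 2.732 | 2.009 | 5.3% | 5.2% |

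With no Bonferroni adjustment the simulated rate is 14.9% at 5%. The control-arm test rejects about 0%. A paired t test using the training arm's own SD holds its level (2.5% and 0.8%).

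**3. Between-arm (group-by-time) test at 5%.** Compare the variance the test uses for the difference in mean change with the true variance.
- 30 v 30: both are 53/30 = 1.767, so the standard error is right. Simulated 5.3%.
- 24 training v 30 control: pooled variance (23×49 + 29×4)/52 = 23.90; times (1/24 + 1/30) = 1.793, against a true 49/24 + 4/30 = 2.175. SE ratio √(1.793/2.175) = 0.91. Simulated 7.9%.
- 30 training v 24 control: (29×49 + 23×4)/52 = 29.10; times (1/30 + 1/24) = 2.182, against a true 49/30 + 4/24 = 1.800. SE ratio 1.10. Simulated 3.4%.
- The Welch test on change rejects 5.0 to 5.1% in all three.

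**4. Literal reading: four independent cells.** The error term now contains the spread of load between children, which the documents do not give. I assume a baseline SD b and a change unrelated to baseline. The average cell variance is then (4b² + 53)/4. For b = 10 W it is 113.25, so the model's SE of the training-arm change is √(2 × 113.25/30) = 2.75 W, against a true 7/√30 = 1.28 W. Simulated rejection of the training-arm test at nominal 5% is 6.4% for b = 3 W, 1.5% for b = 5 W and about 0% for b = 10 W or more.

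**The case against.** **The model is not stated.** A reader might infer that the plan makes the training-arm test reject three to six times too often. The document does not support that as a fact. It calls only the EMG ANOVA repeated-measures, and under the literal reading the error mostly runs the other way. The multiple also depends on unstated choices: the number of comparisons, the post hoc error term, and whether post hoc tests follow only a significant interaction. The threefold figure uses no Bonferroni adjustment, which is not the plan. The sixfold figure is relative to 0.83%, an absolute rate of 5.2%. All of this stands. Repeated measures is still the natural reading, since the same children are measured twice and planning uses their change, but the inflation must be stated conditionally.

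**Gating would protect.** With no change in either arm, a gate on the interaction brings the false training-arm claim to 4.0–5.2% for one to six comparisons. The plan states no gate for this ANOVA. If controls fell by the planned 3 W and training did nothing, the gated rate would be about 5.0% at nominal 2.5% and 2.6% at 0.83%.

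**The null case is assumed.** The 7 W SD is planned alongside a 16 W gain. If training did nothing, nothing in the document says the SDs would still differ. At the planned effect, 16/(7/√30) = 12.5, so significance is not in doubt. Both points stand. They limit the false-positive argument, but not the wrong standard errors when training works as planned.

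**The randomised comparison is sound as planned.** It is, with equal arms. Nothing says that losses would fall mainly on training: both arms have the same session schedule and the exclusion rule covers both. A reader might infer a systematic bias in favour of training, and the documents do not support that. The drift can go either way.

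**The evidence is narrow.** It is one variable from a cited study, with an unlabelled ±. The shuttle has a single SD of 1.6. This stands.

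**Conclusion.** The point holds in limited form. For CPET load, a pooled-error ANOVA conflicts with the plan's own figures. On the repeated-measures reading, within-arm standard errors are 26% too small for training and 2.6 times too large for control. On the literal reading the pairing is lost and the tests are far too conservative at any assumed baseline SD of 5 W or more. Either way the reported precision is wrong.

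The excess false-positive rate in the training arm (about 10% at 2.5%, or 5.2% at 0.83%) needs four assumptions: ± means SD, the ANOVA is repeated-measures with pooled post hoc error, post hoc tests are not gated, and the 7 W SD persists with no true change. The between-arm test is near nominal with the planned equal arms (5.3%) and moves to 7.9% or 3.4% when one arm falls to 24. The expected conclusion at a 16 W gain would not change. It is worth correcting because the remedy is nearly free, but it does not undermine the trial.

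**What to change.** In the Statistical analysis section, for CPET load and preferably for every pre-post outcome:

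- Make the primary test a between-arm comparison of change that allows unequal variances: a Welch test on change, or a linear model with HC3 standard errors. This removes the ambiguity about pairing as well.
- Report within-arm changes descriptively, each with its own arm's SD and confidence interval, in place of pooled Bonferroni pre-post tests.

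The cost is a sentence or two of wording and slightly fewer degrees of freedom. At 30 per arm with these SDs, Welch has about 34 df instead of 58, so the critical value is 2.03 instead of 2.00. Extending the method to the shuttle and the secondary outcomes is a matter of consistency; the plan gives no sign of unequal variances there.

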**Fig 1 Fig1:**
[figure not shown]
Flow of patients through the study

Visit 1: quality of life questionnaire, asthma control questionnaire, pre- and post-bronchodilator spirometry (400 μcg salbutamol), inflammatory assessment (blood collection), and cardiopulmonary exercise test on a cycle ergometer.

Visit 2: Assessment of strength and endurance of the quadriceps femoris and biceps brachii muscles with surface electromyography.

Visit 3: ISWT and an accelerometer will be used to assess physical activity in daily life.

The volunteers will be randomized to receive a pulmonary rehabilitation program (intervention group) or chest physiotherapy plus stretching exercises (control group), as described below by the website randomization.com.

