### Control group

The control group will have chest physiotherapy and stretching exercises twice a week. Each session will be 60 minutes, with a minimum interval of 24 hours, for a period of 8 weeks. For each session, the oral high-frequency oscillation device (Flutter®) will be used for 10 minutes, 5 minutes in each lateral decubitus position, followed by stretching of the upper and lower limbs for 40 minutes. All exercises will be active, performed in sitting and lying positions without increasing the heart rate. The remaining 10 minutes will be used to discuss doubts about the disease and the use of the booklet.

Both groups will be oriented about the disease (proper use of medication, use of peak flow, triggering factors for crisis). On the date of the initial evaluation, they will take home a booklet with the main information about the given guidelines. All volunteers will be reevaluated after 8 weeks, when the same initial assessments will be performed again.

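### The Kruskal-Wallis fallback has no group-by-time term, so for outcomes judged non-Gaussian it does not test the treatment effect and can react to an equal gain in both arms

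*Protocol article*

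**What the plan says.** The Statistical analysis section of the protocol article sets a two-step rule. First, "The data normality will be analyzed using the Kolmogorov-Smirnov test". The main comparison is then fixed as follows: "Comparisons between groups and time (pre- and post-rehabilitation) will be analyzed by two-way analysis of variance (ANOVA), with the Bonferroni test post hoc". The same sentence goes on to name the alternative for data that fail the check: "or by the Kruskal Wallis test, depending on the data adherence or non-adherence to the Gaussian curve". Kruskal-Wallis is thus the named replacement for a two-factor analysis whenever the data are judged non-Gaussian. The threshold is "The value of *P* <0.05 will be set as significant".

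The design is paired. Under Control group the article states: "All volunteers will be reevaluated after 8 weeks, when the same initial assessments will be performed again". A repeated-measures method is named only for the electromyography variables: "Three-way repeated measures ANOVA group vs endurance (0–100 % endurance time, 25 % increments time) vs time (pre- and post". For the other outcomes the article names no change score, no paired rank test and no other non-parametric method for group by time. It also does not say how the data would be laid out for Kruskal-Wallis.

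**The concern.** In a two-arm trial with a baseline and an 8-week visit, the treatment effect is the difference between arms in change from baseline, which is the group-by-time term. Two-way ANOVA contains that term. Kruskal-Wallis does not: it asks whether several independent samples share one distribution. Used for two groups and two times, it has to treat the four cells as four unrelated samples. A small p-value then means only that some cell differs from another, and a change over time common to both arms is enough.

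A shared change is possible here. Controls are also treated: "The volunteers will be randomized to receive a pulmonary rehabilitation program (intervention group) or chest physiotherapy plus stretching exercises (control group"). Both arms attend twice-weekly sessions and use the oscillation device, and "Both groups will be oriented about the disease (proper use of medication, use of peak flow, triggering factors for crisis"). Both repeat effort-dependent tests. If such a change were read as a treatment effect, the trial would credit rehabilitation with something that also happened in the controls.

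The Kolmogorov-Smirnov result also decides which hypothesis is tested for a given outcome: one that includes an interaction, or one that any difference between cells can reject.

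**Working it through.** The plan gives no operating figure for the fallback, so there is none to reproduce. The check is what the named test does with data of this design.

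**Inputs from the protocol article**
- Two arms and two times, so 2 × 2 = 4 cells.
- 30 children per group (Statistical analysis), so N = 4 × 30 = 120 values from 60 children.
- Significance level 0.05.
- Shuttle effect of 2.0 levels with SD 1.6, so 2.0 / 1.6 = 1.25 SD.

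**Assumptions, because the article gives no figure**
- Pre-post correlation 0.5 to 0.9.
- Shared gain in both arms 0 to 0.8 SD.
- A moderate between-arm effect of 0.5 SD.
- Pre and post values bivariate normal. The rejection rate of Kruskal-Wallis on the raw values is the same under any monotone transformation, such as log-normal data, because the test uses ranks only.

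**Hypotheses**
- Treatment effect: (post − pre in intervention) − (post − pre in control).
- Four-cell statistic: H = 12 / [N(N+1)] × Σ(R_j² / n_j) − 3(N+1), where R_j is the rank sum of cell j, referred to chi-square with 4 − 1 = 3 degrees of freedom. Its null is that all four cells have the same distribution.
- If both arms gain δ, the treatment effect is δ − δ = 0, but both post cells are shifted by δ against both pre cells. H grows with δ although there is nothing to find between arms.

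**No treatment effect, 30 per arm** (at least 2,000 simulated trials per setting; Monte Carlo standard error at most √(0.25 / 2000) ≈ 1 percentage point)

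| Shared gain in both arms | Four-cell Kruskal-Wallis rejects | Rank test of change between arms |
|---|---|---|
| 0 | 3–6% | about 5% |
| 0.2 SD | 7–8% | about 5% |
| 0.3 SD | 11–19% | about 5% |
| 0.4 SD | 27–35% | about 5% |
| 0.5 SD | 59–63% | about 5% |
| 0.6 SD | 81–93% | about 5% |
| 0.8 SD | near 100% | about 5% |

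The ranges run over the correlations. The first row separates the causes. With no shared gain the test stays close to its level, although it ignores the pairing there too. The false signal comes from the all-cells-equal null.

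**Power for a 0.5 SD between-arm effect with no shared gain, 30 per arm**

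| Correlation | Four-cell Kruskal-Wallis | Mann-Whitney on change |
|---|---|---|
| 0.5 | 40% | 46% |
| 0.8 | 36% | 83% |
| 0.9 | 36% | 99% |

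This is where the ignored pairing costs something: the higher the correlation, the more information is thrown away. At the protocol's own 1.25 SD shuttle effect, both tests have power near 100%.

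**The case against.** - **Layout.** The article does not say that Kruskal-Wallis will be run on four cells. Applied to each child's change, or between arms at the 8-week visit only, it holds about 5% under an equal gain. The cycle-ergometer sample size is built on pre-post differences per arm, so a change-score reading is possible. This stands as a limit. But the sentence covers groups and time together and mentions no change score, so four cells is the plainer reading. If change scores were meant, the text needs to say so.
- **Shared gain.** It is assumed, and the rejection rate depends on it steeply. The sample-size paragraph takes the control arm's cycle load to change by −3 ± 2 W, a decline, and control exercises are meant not to raise heart rate. This also stands: for that outcome the plan does not expect a shared gain. Education and repeat testing make one more plausible for quality of life or the shuttle walk, but the article gives no size.
- **Scope.** The default is ANOVA. A reader might infer that a primary outcome will end up in the fallback. The article neither says nor implies this; the rule merely does not exclude it.
- **Cause.** A reader might infer that treating paired values as independent produces the false positives. It does not, as the zero-gain row shows.
- **ANOVA branch.** A reader might infer that it should go as well, with baseline-adjusted ANCOVA for every outcome. That may be a reasonable preference, but nothing in this point shows the ANOVA branch to be wrong.

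**Conclusion.** The point holds in a bounded form. The plan names, as substitute for a two-factor comparison of paired data, a test that has neither the second factor nor the pairing. On the plain four-cell reading it does not answer whether rehabilitation beats control, and an equal gain in both arms can be reported as significant. How often depends on an unknown: hardly above 5% for a shared gain of 0.2 SD, more often than not at 0.5 SD, almost always at 0.8 SD. It would therefore be too strong to say that the fallback will declare significance whenever both arms improve. Separately, it loses power for moderate effects when the correlation is high, but not for an effect as large as the one in the shuttle calculation.

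These sizes rest on 30 per arm, the assumed correlations and gains, and the four-cell layout. The defect touches only outcomes that fail the Kolmogorov-Smirnov check. The mismatch between test and question rests on none of the assumed values. It should be fixed, but because it is conditional it does not by itself undermine the trial.

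**What to change.** In the Statistical analysis section, replace the Kruskal-Wallis fallback with a between-arm test of the treatment effect that uses each child's baseline: either Mann-Whitney on change from baseline to 8 weeks, or rank ANCOVA of the 8-week value on baseline. State that this comparison, and not any pre-post test within an arm, is the test of treatment.

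Preferably also name the analysis for each outcome in advance, so that the hypothesis tested does not hang on a normality test of the trial data.

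The cost is wording in one section. No data are needed beyond the baseline and 8-week assessments already planned. The Trial status section reports that recruitment is still under way, so the change can be made before any between-arm analysis.

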### Outcomes

The primary outcome will be the physical capacity assessed by the cardiopulmonary exercise testing and ISWT. The secondary outcomes will be quality of life, peripheral muscle strength, and inflammatory markers.

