#### Surface electromyography (*s*EMG)

The surface electromyographic (sEMG) will be recorded in the dominant upper and lower limb. Active bipolar surface electrodes will be positioned in the belly of the evaluated muscles (RF and BB) as previously described [34]. The *s*EMG (EMG System, model EMG800C, São José dos Campos, Brazil) will be recorded using a 4-channel device (EMG System do Brazil Ltda®), with a band pass filter with cutoff frequencies of 20 to 500 Hz, an amplifier gain of 1000, and a common rejection mode ratio >100 dB. All data will be acquired and processed using a 12-bit analog-to-digital converter, with a sampling frequency of 2 kHz. The obtained signal will be amplified and converted to digital format for data recording and analysis.

The sEMG signal will be divided into 1-second windows and the root mean square (RMS) and median frequency (MDF) of the power spectrum will be calculated for each window. Five consecutive values over RMS time and MDF will be averaged to obtain mean values corresponding to 0, 25, 50, 75, and 100 % of the endurance time. All EMG signals will be processed performing specific routines carried out in the Matlab program, R2010b (The MathWorks Inc., Natick, MA, USA).

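### Student–Newman–Keuls after the three-way EMG ANOVA does not hold the familywise error at 5%, and the family of comparisons is not defined

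*Protocol article*

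**What the plan says.** The Statistical analysis section of the protocol article specifies, for the EMG variables, a "Three-way repeated measures ANOVA group vs endurance (0–100 % endurance time, 25 % increments time) vs time (pre- and post" design. The follow-up is "post hoc Student–Newman–Keuls pairwise comparisons, when appropriate". The threshold for every test in the section is P "<0.05 will be set as significant".

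The section on surface electromyography fixes the endurance factor. Root mean square (RMS) and median frequency are each reduced to "mean values corresponding to 0, 25, 50, 75, and 100 % of the endurance time", which gives five levels. Two muscles are recorded, so there are four such analyses (two variables in two muscles).

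For the simpler two-way ANOVA (group by pre/post), the same section plans comparisons "with the Bonferroni test post hoc". It states no other control of multiplicity for the EMG comparisons.

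The Outcomes section names physical capacity as primary and then says: "The secondary outcomes will be quality of life, peripheral muscle strength, and inflammatory markers". RMS and median frequency are not listed by name.

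**The concern.** SNK is a step-down range test. It compares the range of any p ordered means with the critical value for p means, not for all the means in the family. Each separate set of truly equal means therefore gets its own test at about 5%, and the chances of a false positive add up across sets.

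The design makes that situation plausible. Endurance is a factor in the model because the EMG signal is followed through a contraction held to the limit of tolerance. Suppose the signal drifts along that contraction and training does nothing. At each endurance point the four cells (two groups, before and after) are then equal, and the five points differ. That gives five separate equal sets.

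At stake is how the EMG results are read. The Background presents EMG-based assessment of muscle strength and endurance in asthmatic children as new. An isolated difference between cells at one endurance point could be reported as a training effect when the real error rate is above the stated 5%.

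**Working it through.** The 0.05 in the plan is a threshold, so there is no derived figure to reproduce. The check compares it with the familywise error of SNK.

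**Inputs**
- Levels: group 2, endurance 5, pre/post 2 (Statistical analysis; Surface electromyography). Cells: 2 × 5 × 2 = 20. Possible pairs: 20 × 19 / 2 = 190.
- Alpha: 0.05 (Statistical analysis).
- Children per cell, used only for the error degrees of freedom in the simulation: 27, from "the sample size needed was 27 patients in each group".
- Assumed for the simulation: independent cells with a common error variance, and gaps between endurance points of 0.5 SD, 1 SD or much wider (10 SD).

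**Step 1. Formula.** If the true means form m well-separated sets of equal means, each set is tested at about 5%, and

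familywise error ≈ 1 − 0.95^m.

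A set needs at least two means, so for k means the largest m is k/2 rounded down. With k ≤ 3, or with only one set of equal means, m is at most 1 and the error stays at 5%.

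**Step 2. Ceilings by size of family**
- k = 2: 1 − 0.95 = 5.0%
- k = 4 or 5: 1 − 0.95² = 9.75%
- k = 10: 1 − 0.95⁵ = 22.6%
- k = 20: 1 − 0.95¹⁰ = 40.1%

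**Step 3. Endurance effect only, all 20 cells in one family.** There are five sets of four equal cells, so m = 5 and the limit for wide gaps is 1 − 0.95⁵ = 22.6%.

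**Step 4. Simulation** of the SNK procedure with studentized-range critical values: 4,000 runs, n = 27 per cell, df = k(n − 1), which is 20 × 26 = 520 for 20 cells. Tukey and Bonferroni over all pairs were applied to the same data.

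| True means | SNK | Tukey | Bonferroni |
|---|---|---|---|
| 20 cells, all equal | 4.9% | 4.9% | 3.6% |
| 20 cells, five sets of four, wide gaps | 22.1% | 1.3% | 0.9% |
| 20 cells, five sets of four, 1 SD gaps | 22.2% | 1.1% | 0.7% |
| 20 cells, five sets of four, 0.5 SD gaps | 11.7% | 1.1% | 0.6% |
| 20 cells, two sets of ten | 10.0% | 3.1% | 2.0% |
| 20 cells, ten equal pairs | 39.2% | 0.35% | 0.25% |
| 10 means, five equal pairs | 21.6% | 0.8% | 0.6% |
| 5 means, two equal pairs and one apart | 10.0% | 1.3% | 0.9% |
| 4 means, two equal pairs | 9.3% | 2.0% | 1.6% |
| 3 means, one equal pair and one apart | 4.9% | 1.7% | 1.4% |

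The Monte Carlo standard error at 22% is √(0.22 × 0.78 / 4000) = 0.65 percentage points, so the simulation agrees with the formula. Each figure is for one muscle and one EMG variable.

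**The case against.** Several points can fairly be made for the plan.

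- **Drift alone does not inflate the error.** A reader might infer that SNK holds 5% only when all means are equal. That is too strong: it also holds with at most three means, or with a single set of equal means. If the signal changes steadily, all five endurance means differ, and no true null is left among them to reject falsely. This stands. The excess appears when equal cells recur at several endurance points, or when endurance means are equal in separate pairs.
- **The family is not stated.** A reader might take 40% as the error rate of this plan. The article does not support that: the figure needs all 20 cells in one family, arranged as ten well-separated equal pairs. This also stands.
- **Follow-up is conditional.** The qualifier ending the SNK phrase may mean that pairs are tested only after a significant F-test. This helps only in part. A real endurance effect makes the endurance term significant, and the article does not say which term must be significant before which means are compared.
- **Within-child correlation.** A reader might infer that the plan treats repeated measurements as independent. It specifies a repeated measures ANOVA and is silent on the post hoc error term, a detail that an article can leave to the full plan. Silence does not show that the correlation is ignored.
- **Bonferroni elsewhere.** Different post hoc tests for different models are not a contradiction. The two-way ANOVA only shows that an adjusted method is already in use.
- **Low stakes.** EMG is at most a companion to the strength tests. This stands and limits the importance of the point.

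**Conclusion.** The point holds as a minor one. SNK does not strongly control the familywise error for the EMG comparisons at the stated 5%, and the article names no other control for them.

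The size depends on a family that the article leaves open:
- a two-level factor alone: no inflation;
- the five endurance levels alone: at most 9.75%, and only if they form two equal pairs;
- all 20 cells with an endurance effect only: about 12% to 22%, for gaps of 0.5 SD and upward;
- all 20 cells in the extreme arrangement: up to 40%.

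The simulated figures assume independent cells and a common error. Correlation within a child would change them, but it does not give SNK strong control.

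A reader might also infer that the trial's main result is at risk. It is not: EMG is not a named primary or secondary outcome, and SNK plays no part in the sample size.

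**What to change.** Replace SNK with Holm- or Bonferroni-adjusted contrasts.

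- **Training-effect family:** for each muscle and variable, the between-group difference in pre-post change at each of the five endurance points. Bonferroni would test each at 0.05 / 5 = 0.01. Holm starts at 0.01 for the smallest P value and then relaxes.
- **Error terms:** suited to the within-child factors, endurance and pre/post.
- **No gate on the group by time term.** An effect confined to some endurance points would appear in the three-way interaction, and such a gate could block it. Holm or Bonferroni controls the error over the five contrasts without a gate.
- **Comparisons across endurance points:** if any are kept, name them and adjust them in the same way as a separate family. All pairs of five points would be 5 × 4 / 2 = 10 comparisons.

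The cost is slightly less power for the EMG comparisons. The change alters the follow-up analysis and not only its description, so it should be fixed before the EMG data are analysed. The primary analysis and recruitment do not change.
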